### 9.4.3 Safety/Tolerability Outcome Variables

No further safety variables were assessed. The extent of exposure is indirectly assessed via the separate survey of the clinical project management. In this, the site-specific use of disinfection [`Desinf_Verb`] and the site-specific costs for gloves and gowns [`Kosten`] are recorded. These will be summarized per phase.

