# Study protocol of the cluster-randomized, cross-over, non-inferiority BALTIC trial

## Synopsis

**Background:** There is an urgent need to optimize and evaluate infection prevention and control (IPC) strategies for the care of highly vulnerable infants. Several infection outbreaks in German neonatal intensive care units (NICUs) required rapid responses by hospitals and improved future preparedness. As a consequence, German authorities recommended weekly colonization screening on NICUs. This screening aims to detect multidrug-resistant organisms (MDRO) and bacteria with high transmissibility. According to these guidelines, infants colonized with multiresistant gram-negative (MRGN) bacteria with *in-vitro* resistance to piperacillin and cephalosporins (2MRGN) should be cared wearing non-sterile gloves and gowns in addition to standard hygiene precautions. Whether these extended IPC measures have an individual benefit for infants or contribute to the prevention of infection outbreaks is unknown.

**Acronym:** BALTIC Barrier protection to lower transmission and infection rates with Gram-negative 2-MRGN in preterm children

**Design:** Multicenter, cluster-randomized controlled trial with cross over after 12 months

**Population:** infants requiring neonatal intensive care

**Intervention:** Focus on hand disinfection for the care of 2MRGN colonized infants in NICUs

**Control:** Current standard hand disinfection + gloves and gowns (barrier care) for the care of 2MRGN colonized infants in NICUs

**Outcome:** rate of healthcare-associated (HA) Gram-negative bloodstream infections

**Methods:** NICUs will be screened for participation and randomly allocated to two trial arms: receiving the intervention "standard precautions with a special focus on hand disinfection" or control (standard precautions "plus" barrier care) for the care of 2MRGN positive infants. Cross over will be performed after 12 months for another 12 months per site. Secondary outcomes included transmission rate with screening relevant bacteria, overall rate of clinical and culture-proven infections, number of antibiotic cycles and disinfectant use. Regular trainings and hygiene audits are standardized co-interventions.

According to our single center data, 9.3% of NICU-treated infants are colonized with 2MRGN during their hospital stay.

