### *Audits*

Quality controls and data security are ensured by the availability of a study protocol, by a monitoring visit prior to the start of the study and by standard operating procedures (SOP, e. g. for diagnosis of sepsis, transmission). Audits are initiated to verify adherence to the study protocol and ICH-GCP (Good clinical practice) procedures.

In order to evaluate the compliance with infection control measures, direct observations are planned on a random basis by the study team and IPC nurses. The observations will not affect

other treatment priorities, e.g. kangaroo care. We aim for anonymous documentation of disinfectant use (nurse, doctor, service staff, parents, others), and compliance with 5 moments of proper hand hygiene, use of gloves and long-sleeved gowns. The Hawthorne effect, i.e. alteration of typical behavior by being observed and variability among observers (external representatives of the study leadership, local hygiene experts, and link nurses) is a potential disadvantage of the direct observation approach (25). We therefore collect data on disinfectant use in the clusters (mL per patient day) which serves as a surrogate for hygiene compliance.

Management of transmissions and possible outbreaks will be at the discretion of the local team based on NICU guidelines which was different across the NICUs. The local standards are documented at initiation of the study-centers, at after 12 months (cross-over) and at the end of the study after 24 months. In the manuscript reporting data we will also report on extended hygiene measures and additional tests for outbreak identification (e.g., genotyping, pulse field electrophoresis)

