### *Outcomes*

The primary endpoint is the rate of HA bloodstream infections with Gram-negative pathogens in all preterm and newborn infants who received colonization screening. This outcome is defined clinically according to NEO-KISS criteria (at least two clinical signs of sepsis + one laboratory sign, e.g. increase in C-reactive protein > 10mg/l) after 72 hours of life and requires the detection of a Gram-negative pathogen in the blood culture. Blood-culture isolates will be sent from the study centers to the study management.

Key secondary endpoint is the 2MRGN transmission rate which is assumed if another infant is colonized with the same 2MRGN pathogen after 2MRGN colonization or infection of an infant

requiring intensive care in a temporal (maximum 90 days) and spatial context (potential contact in the intensive care unit) (26). This assumption is made if, in addition to pathogen identification, the antimicrobial susceptibility testing patterns are identical. Suspected transmission of or bloodstream infection with an 2MRGN pathogen will be reported to the study management as severe adverse event within 24 hours.

Transmission/outbreak management remains the responsibility of the local interdisciplinary infection control team and is carried out according to local standards, including the decision whether to initiate genetic identity testing in the acute situation. 2MRGN isolates will be shipped from local sites and molecular typing will be performed at the Department of Infectious Diseases and Medical Microbiology at the University of Lübeck. Other secondary outcomes at the level of study sites per period ("study phase") are:

- Rate of clinical and culture proven infections
- Rate of infection outbreaks
- Number of initiated antibiotic cycles
- Duration of antibiotic treatment (days)
- Exposure to reserve antibiotics, including Carbapenems per study site in % infants.

To assure documentation of relevant outcomes, intensive interdisciplinary collaboration (neonatology/infectiology/hygiene/pharmacy/management) is required. Data are collected by monthly cluster report forms on infection and transmission rates and yearly surveillance of antibiotic use, disinfectant consumption, and cost estimations.

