To allow for patient-level description, the data set is re-structured to contain one line per patient based on the documented number of patients admitted to the site [Aufnahmen\_Neo]. In this, the following month-level variables are used to construct the following patient-level variables indicating presence or absence of the event:

| Variable                                     | Month-level
(original variable) | Patient-level
(constructed variable) |
|----------------------------------------------|------------------------------------|-----------------------------------------|
| Gram negative infection                      | Anzahl_gramNeg_nurLOS              | gramNeg_nurLOS                          |
| At least one suspected transmission          | Transm_Patient                     | Transm                                  |
| At least one suspected transmission of 2MRGN | Transmission_2MRGN_Patient_SAE     | Transm2m                                |
| Clinical infection                           | Anzahl_kl_Sepsis_allg              | Sepsis                                  |
| Any BSI                                      | Anzahl_BKpos_Sepsis_allg           | Sepsis_pos                              |
| 2MRGN BSI                                    | Anzahl_2MRGN_LOS                   | LOS                                     |

For the estimation of the GEE models, a cluster variable [Cluster] is created that combines the information from the site identifier [Klinik\_ID] with the variable indicating the phase [Randomisierung], so that every site corresponds to two clusters, one for every phase.

The variable counting the number started reserve antibiotics in a month [Anzahl\_beg\_Reserve\_ATB] is dichotomized to indicate whether at least one treatment with a reserve antibiotic was started or not [Beg\_Reserve\_ATB].

In addition, the clinical project management team surveys the participating sites about consumption of disinfectant and estimated costs. This data will separately be transferred to the IMBS for analysis.

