| Adjustments for covariates                       | None                                                                                                                                                                                                                                                                                                                                                                                                                                                                                                                                                                                                                                                                                                                                                                                                                                                                                                                                                |
| Main estimator                                   | 
Risk difference is estimated from a GEE logistic regression model with identity link using the following command from the R-library geepack:
 <pre>geeglm(cbind(Anzahl_gramNeg_nurLOS, Anzahl_gramNeg_nurLOS_negativ) ~ Randomisierung, family = binomial(link = "identity"), id = Cluster, corstr = "independence")</pre> 
with the variable <code>Randomisierung</code> indicating the phase (CO vs. IV)
 
From this model, the 95% confidence interval for the risk difference and the one-sided p-value are estimated.
                                                                                                                                                                                                                                                                                                                                                                                                         |

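### Disinfectant use is only summarised per phase, with no IV/CO estimate or interval, and the documents disagree on whether it is a secondary outcome

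*Combined protocol and SAP*

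**What the plan says.** The variable has a different status in different places.

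- **Protocol, Synopsis (Methods):** "Secondary outcomes included transmission rate with screening relevant bacteria, overall rate of clinical and culture-proven infections, number of antibiotic cycles and disinfectant use".
- **Protocol, Outcomes:** the list introduced by "Other secondary outcomes at the level of study sites per period" covers infections, outbreaks, antibiotic cycles, antibiotic duration and reserve antibiotics, but not disinfectant. Disinfectant appears only in the closing sentence on data collection: "yearly surveillance of antibiotic use, disinfectant consumption, and cost estimations".
- **Protocol, Audits:** "We therefore collect data on disinfectant use in the clusters (mL per patient day) which serves as a surrogate for hygiene compliance".
- **SAP 4.1:** the secondary endpoints do not include it.
- **SAP 5:** it comes from a survey of the sites, and "This data will separately be transferred to the IMBS for analysis". No method is named there.
- **SAP 9.4.3:** it is an indirect measure of the extent of exposure, recorded with glove and gown costs. The whole analysis is "These will be summarized per phase".

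Three other statements bear on this. The protocol's statistical section says that secondary endpoints are analysed like the primary one, per individual or per cluster. The secondary variables modelled in SAP 9.4.1 and 9.4.2 each get an estimate with a 95% confidence interval. In the SAP's models the regimen variable is described as "indicating the phase (CO vs. IV"), so a summary per phase is a summary per regimen.

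**The concern.** The intervention is described as standard precautions with a particular focus on hand disinfection, and the protocol's rationale argues that glove use can displace hand hygiene. Readers of a non-inferiority result will ask whether hand disinfection differed between the phases. Disinfectant volume is the only hand-disinfection measure that the SAP handles. SAP 5.2 reports the share of patients not treated as randomised, which is a different question.

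Two summaries side by side let a reader subtract one from the other but give no measure of the uncertainty of the difference. The design could supply one, because every site contributes both regimens. The unsettled status matters because it decides what is owed. If the synopsis governs, a summary alone falls short of the protocol's own rule for secondary endpoints. If the Audits section governs, a summary is defensible and the synopsis needs correcting.

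**Working it through.** The documents give no figure for disinfectant use, so there is nothing to reproduce. Three things can be checked.

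**1. What the per-phase summary already gives.** There are 12 sites, each with one IV and one CO phase (SAP 4.1 and 5). Collection is yearly (protocol, Outcomes) and a phase lasts 12 months, so I take one value per site and phase; this is an inference. With complete pairs,

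mean of log(IV) − mean of log(CO) = (1/12) × Σ [log(IV) − log(CO)],

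so the difference in phase means is exactly the mean within-site difference. The same holds on the raw scale. Site levels cancel. The equality fails only if a site lacks one phase, or if medians are reported. What the summary lacks is the interval.

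**2. How precise a within-site comparison would be.** The documents give no SD, so I assume a within-site SD of log use, sw, of 0.10 to 0.15. For each site take d = log(IV) − log(CO), which has SD √2 × sw. Regress d on phase order coded +1/−1, leaving 10 df. With 6 sites in each order:

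half-width = t(0.975, 10) × √2 × sw / √12, with t(0.975, 10) = 2.228.

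| sw | SE | half-width (log) | interval for the ratio | P(95% CI excludes 1) at true ratio 1.15 | ratio needed for 80% |
|---|---|---|---|---|---|
| 0.10 | 0.0408 | 0.091 | ×/÷ 1.095 | 0.87 | 1.14 |
| 0.15 | 0.0612 | 0.136 | ×/÷ 1.146 | 0.54 | 1.21 |

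The probabilities come from the noncentral t distribution, with noncentrality log(1.15)/SE = 0.1398/0.0408 = 3.42 and 0.1398/0.0612 = 2.28.

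*Why an order term.* SAP 4.1 describes a simple sequence tool, so a 7/5 split of orders is possible. If use drifted by an assumed 0.10 on the log scale from the first phase to the second, the unadjusted mean difference would be off by (7 − 5)/12 × 0.10 = 0.017, about 1.7%. Adjusting at 7/5 widens the interval by 1.4% compared with 6/6.

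*Why the site and not the SAP's Cluster.* SAP 5 defines Cluster "so that every site corresponds to two clusters, one for every phase". With that unit a site's two values count as unrelated and the pairing is lost. In units of the SD of a single site-phase value, and without the order term, the 95% half-width over 12 pairs (11 df) depends on the assumed within-site correlation:

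| correlation | 0 | 0.3 | 0.5 | 0.7 | 0.9 |
|---|---|---|---|---|---|
| paired | 0.90 | 0.75 | 0.64 | 0.49 | 0.28 |
| treated as 24 separate units | 0.85 | 0.85 | 0.85 | 0.85 | 0.85 |

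Pairing is the better choice at each tabulated correlation of 0.3 or more, and slightly worse at zero.

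**3. What the figure cannot show.** The protocol expects about 10% of infants to be colonised with 2MRGN. If use fell by an assumed 20% to 40% for those infants only, and they account for 10% of use, the unit total falls by 0.20 × 0.10 = 2% to 0.40 × 0.10 = 4%. The interval would exclude 1 with probability 0.07 to 0.15 at sw = 0.10, and 0.06 to 0.09 at sw = 0.15.

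**The case against.** In the SAP's favour, it follows the detailed Outcomes section rather than one sentence of the synopsis, a plain summary is ordinary practice for an exposure or compliance variable, and all secondary analyses are descriptive anyway. The unit is in the protocol, to which the SAP refers. Antibiotic cycles are an imperfect comparator, since they are in the Outcomes list and recorded monthly. Most of this stands, and it is why the point is minor. It does not settle the conflict with the synopsis, and a descriptive analysis can still carry an interval, as the other descriptive secondary analyses do.

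A reader might infer three stronger things that the documents do not support.

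- *That the per-phase summary confuses the regimen difference with differences between sites.* With complete pairs it does not; the identity in step 1 shows that site levels cancel.
- *That the plan yields an interval several times too wide.* The SAP plans no interval for this variable, paired or unpaired. The comparison of units in step 2 only supports the choice of unit for an added interval.
- *That hand hygiene is otherwise unassessed.* The protocol plans random observations of compliance at 6, 12, 18 and 24 months, and direct observation of the five moments and of glove and gown use. Disinfectant volume is collected because such observation is open to the Hawthorne effect. The SAP does not analyse these observations, but section 2 limits it to the analyses for which the statistics institute is responsible, so their absence there does not mean that they go unreported.

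**Conclusion.** The point holds as a minor one. The documents give disinfectant use conflicting status, and the SAP plans no between-regimen estimate or interval for it, although the cross-over provides 12 within-site pairs. The SAP therefore cannot say how precisely any difference in use is known.

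Under the assumed within-site SDs, a paired interval of about ×/÷ 1.10 to 1.15 is within reach. That would show a unit-wide shift of roughly 14% to 21% with 80% probability. These figures rest on assumed SDs, on one value per site and phase, and on 12 complete pairs.

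A ratio near 1 should not be read as evidence about the care of colonised infants, because a change confined to them would almost always go unseen. The primary non-inferiority conclusion does not depend on this variable.

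**What to change.** In SAP 9.4.3:

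1. State whether disinfectant use is a secondary outcome or a compliance surrogate, and bring the synopsis, the Outcomes section and SAP 4.1 into line.
2. Give the unit: mL per patient day, one value per site covering each 12-month phase.
3. Keep the per-phase summary and add a descriptive comparison. For each site compute log(IV) minus log(CO) and regress it on phase order coded +1/−1. Report exp(intercept) as the IV/CO ratio with a 95% t-interval (10 df with 12 complete pairs) and the number of complete pairs.
4. Say that the site is the unit here, not Cluster.
5. State that the figure covers the whole unit and cannot show a change confined to colonised infants. Refer to the protocol's direct compliance observations and say where they will be reported.

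The cost is a few lines of SAP text and one calculation on data already due to go to the institute, with no new collection. The gain in precision from pairing is small if sites differ little in use, and the ratio says little about the care of the infants whom the intervention targets.

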## 10 Software

For analyses, SAS version 9.4 and R Version 4.1.3 or higher will be used.
